#### RCT sample size calculation

We anticipate there being at least 200 eligible patients per year in total from all three recruitment settings. We assume that not all patients who have been injecting LMWH for five months will agree to continue for a further six months. We are not sure what proportion of patients will be willing to be randomized, but we consider that at least 30% will need to agree in order to make a phase three RCT worthwhile. Therefore, the ALICAT study will aim to assess the feasibility of randomization by determining if at least 30% of potential patients will agree to randomization. We will then calculate the precision of this proportion with a 95% confidence interval. We will also estimate the proportion of patients who experience recurrent VTEs during follow up, which will inform the design of the phase three RCT.

If less than 15% of eligible patients agree to take part in the trial, a phase two RCT may not be suitable as we may not be able to recruit suitable numbers, given that a larger phase three RCT could have more stringent eligibility criteria as a result of this feasibility study. If at least 30% agree to take part, then we would consider that randomizing patients to a larger phase three trial would be feasible. Using a Fleming’s single stage design, setting p1 to 0.15 and p2 to 0.3, and with 5% significance and 90% power, then we will need to approach 62 eligible participants with details of the trial. This design requires that at least 15 out of 62 participants consent to the trial. We therefore propose a two-stage sample size. If at least 15 out of the first 62 participants recruited to the trial accept randomization, then we will continue recruitment into stage two. If fewer than 15 patients agree, we will determine at this stage that randomization within this population is not feasible.

If we expect that 200 will be the maximum potential number of eligible patients, then we can expect to be able to produce a 95% confidence interval for the percentage willing to be randomized of width 13.7% or less. For example, if the percentage is 50%, then we could expect the 95% confidence interval to be 43.15 to 56.85%. If the percentage is 30% we can expect a slightly smaller confidence interval of 23.7 to 36.3%. If only 150 patients are deemed eligible, then we can expect to calculate a 95% confidence interval for 50% randomized of 42.1 to 57.9%.

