Our target registration number for this feasibility trial is therefore 200 patients, of which we hope that at least 60 patients will be randomized into the two groups. Thirty patients per arm will provide enough power to create a 95% confidence interval around the risk of VTE recurrence, which would have a width of 34% or less. As an example, if we found that the risk of VTE occurrence was 50% in the arm that stopped, we would be able to estimate a confidence interval of approximately 33% to 67% or smaller. If the risk of VTE were 8%, the confidence interval would be 0 to 19%.

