#### Statistical analysis

All analyses will be performed on a full intention-to-treat basis, (all patients randomized will be included) and all patients will be analyzed according to their allocated group, whichever treatment they received. We will calculate the percentage of registered patients who were randomized, with 95% confidence interval. We will also calculate the percentage of patients experiencing recurrent VTE recurrence and bleeding events in both groups with 95% confidence intervals. The percentage of patients who died within six months of randomization will be calculated in both arms, along with the percentage of patients who successfully completed six months of trial treatment in the LMWH group. The median QLQ-C30 raw and linear transformed functional scales will be calculated and presented for both arms of the study. No formal subgroup analyses are planned. However, if any treatment effect is found we will investigate whether it is consistent across participant subgroups (defined by all pre-treatment factors collected) although this analysis will be exploratory in nature. Exploratory analyses may be conducted to aid hypothesis generation if a phase three RCT is subsequently developed.

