### Outcome measures

The primary outcome measures are: the number of eligible patients identified over 12 months, the number of recruited patients (randomized participants) over 12 months (target recruitment rate of 30% of eligible patients), and the proportion of participants with recurrent VTEs during trial follow up. VTE will be objectively confirmed through radiological investigation. DVT will be confirmed through Doppler ultrasonography or venography. PE shall be confirmed through a computerized tomography (CT) pulmonary angiogram. The secondary outcome measures are: completion of trial protocol, quality of life, symptom assessment, patients’ and relatives’ experiences of taking part in the trial, and the attitudes of clinicians towards the ALICAT trial.

Completion of trial protocol will be assessed six months after randomization to ascertain the attrition rate due to patient choice or death during the study period. Participants choosing to withdraw from either arm of the study protocol will be invited to participate in a qualitative interview to explore their reasons for withdrawal.

Quality of life will be measured using the EORTC QLQ-C30 Version 3.0 and EQ-5D-5 L at three monthly intervals for six months. The EORTC QLQ-C30 [39], Version 3.0, has become a benchmark measure of quality of life in patients with cancer. It contains five functional scales (physical, role, cognitive, emotional and social), three symptom scales (pain, nausea and/or vomiting, and fatigue), global health and quality of life scales, and several other single items. The EQ-5D-5 L [40] is a short quality of life tool, designed to complement other measures and is recommended by the National Institute for Health and Care Excellence for use in economic analyses [41]. The ALICAT study will identify key cost drivers to inform the design of a future definitive phase three trial, which will include a cost utility study. Orders of magnitude of differences in costs and outcomes identified in the EQ-5D-5 L will help in the estimation of anticipated effect sizes for the full trial.

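### The stage-one rule is derived on eligible patients approached but worded on patients recruited, and the 30% target (eligible) and its planned analysis (registered) use different denominators

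*Protocol article*

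**What the plan says.** All references are to the protocol article.

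**Stage-one rule (RCT sample size calculation).** The design inputs are "setting p1 to 0.15 and p2 to 0.3, and with 5% significance and 90% power". From these the article concludes that "we will need to approach 62 eligible participants with details of the trial", and adds: "This design requires that at least 15 out of 62 participants consent to the trial". The operating rule then reads: "If at least 15 out of the first 62 participants recruited to the trial accept randomization, then we will continue recruitment into stage two". The sentence after it declares randomization not feasible if under 15 patients say yes.

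**Meaning of recruited, and the target (Outcome measures).** One primary outcome is "the number of recruited patients (randomized participants) over 12 months (target recruitment rate of 30% of eligible patients". Recruited therefore means randomized, and the 30% refers to eligible patients. The sample size section sets the same 30% on potential patients.

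**Planned analysis (Statistical analysis).** "We will calculate the percentage of registered patients who were randomized, with 95% confidence interval".

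**How patients move through the study (Participant recruitment).** Patients who look suitable are registered before consent, and a baseline assessment after consent confirms all the criteria. The text following Table 1 says that the study will log, as separate items, whether each potentially eligible patient was in fact eligible, was approached and agreed to randomization, with reasons for non-approach where available.

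**Overall numbers (RCT sample size calculation).** The registration target is 200, "of which we hope that at least 60 patients will be randomized into the two groups".

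**The concern.** The proportion willing to be randomized is the main feasibility result and helps decide whether a phase three trial follows. Two things about it are stated inconsistently.

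First, the stop/continue rule counts a different group from the one its sample size was derived for. If recruited is read as the article defines it elsewhere, the rule does not test willingness to be randomized.

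Second, the target and the analysis that should be compared with it have different denominators. Registered patients can include some later found ineligible, which lowers the rate. Eligible patients can include some never approached, so a rate among those approached can be higher than the rate among all eligible. The Background expects that clinicians may find stopping anticoagulation counter-intuitive, so non-approach is foreseeable. With the denominator open, the same counts could be reported as meeting or missing 30%.

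**Working it through.** **1. Reproduce the 62 and 15.** Inputs from the sample size section: p1 = 0.15, p2 = 0.30, 5% significance, 90% power. Sidedness is not stated. Fleming's normal approximation, one-sided:

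- n = [(1.645 × √(0.15 × 0.85) + 1.282 × √(0.30 × 0.70)) / 0.15]² = [(0.587 + 0.587) / 0.15]² ≈ 61.3, rounded up to 62.
- Threshold: 62 × 0.15 + 1.645 × √(62 × 0.15 × 0.85) = 9.30 + 4.62 = 13.92, rounded to 14, plus 1 = 15.

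Both figures reproduce. A two-sided 5% level would give 73.6, that is 74, which does not match. Exact binomial properties of 15 out of 62 are: chance of continuing 0.038 at a true rate of 15% and 0.873 at 30%. (The shortfall from 90% comes from the normal approximation and is not part of this point.) The calculation is therefore sound for 62 eligible patients approached.

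**2. Apply the rule as worded.** With recruited = randomized, 62 of 62 have accepted, so the chance of continuing is 1 at any true acceptance rate. The timing would also be late: 62 / 0.30 ≈ 207 eligible patients are needed at 30% and 62 / 0.15 ≈ 413 at 15%. The article works with 200 eligible patients.

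If recruited were instead taken to mean consented, the chance of at least 15 of 62 exceeds 0.9999 once half of the consenters go on to accept. The rule would still test little.

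**3. Compare the denominators of the 30%.** The article does not give the share of eligible patients who are approached. Taking it, as an assumption, from 50% to 100%, and setting acceptance among those approached at 30%:

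| Share of eligible approached (assumed) | Randomized / eligible = 0.30 × share | Chance of ≥15 of 62 if the 62 were all eligible patients, approached or not |
|---|---|---|
| 50% | 15% | 0.04 |
| 70% | 21% | 0.31 |
| 80% | 24% | 0.53 |
| 90% | 27% | 0.73 |
| 100% | 30% | 0.87 |

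In the other direction, 60 randomized out of 200 eligible (30%) is 60 / (200 × share) of those approached: 60%, 43%, 37.5%, 33% and 30% for the same five shares.

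For registered against eligible, 60 randomized out of 200 registered is 30%. If 90% of those registered were eligible (assumed), the same 60 would be 60 / 180 = 33.3% of eligible patients. The three denominators agree only if every registered patient is eligible and approached.

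**The case against.** The strongest reply is that the intent is clear. The sentences before the rule speak of approaching 62 eligible patients and needing 15 to consent. The sentence after it, on what happens if too few agree, makes no sense if all 62 are already randomized. The absurd result appears only when the definition in Outcome measures is carried into the sample size section. This stands: the stage-one denominator can be inferred. It does not excuse the wording of a stopping rule, and it does not settle the 30% criterion, where two sections name different denominators.

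A second reply is that registered is close to eligible. The sample size section moves from 200 eligible straight to a registration target of 200, and primary care records are screened against the criteria before patients are invited. The gap may well be small, but full eligibility is still confirmed only after consent.

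A third is that nothing is hidden. The log captures eligibility, approach and agreement, and the number of eligible patients is itself a primary outcome. This also stands, and it is why the repair is cheap.

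Three stronger readings should be resisted.

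- A reader might infer that the literal rule can never be reached because 62 exceeds 60. The 60 is a hoped-for minimum, not a cap.
- A reader might infer that the feasibility verdict will turn on the denominator. The article gives no counts from which to show that.
- A reader might want to apply 15 of 62 to all eligible patients, approached or not. That changes the quantity tested. At an assumed 70% approached and 30% acceptance, the chance of continuing falls from 0.87 to 0.31.

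**Conclusion.** The point holds as two conflicts in stated text, not as missing detail. The stage-one rule contradicts its own derivation: read with the article's definition of recruited, it is met by definition and does not test willingness, although the intended reading can be recovered from the sentences around it. The 30% target and its planned analysis have different denominators, and the article's own procedures show that these groups can differ.

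The 62/15 design is not in question. The effect on the 30% comparison depends on unstated counts: over an assumed 50% to 100% of eligible patients approached, 30% acceptance among those approached is 15% to 30% of eligible patients.

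**What to change.** 1. In RCT sample size calculation, reword the rule as: at least 15 of the first 62 eligible patients approached agree to randomization. This keeps the Fleming calculation unchanged.
2. In Statistical analysis, calculate randomized over eligible, with its 95% confidence interval, so that it matches the target in Outcome measures. Use the same term where the sample size section sets the 30% on potential patients, and take eligibility from the screening log.
3. Report randomized over approached and approached over eligible alongside, so that reluctance of patients can be told apart from non-approach.

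The cost is wording changes and two extra reported proportions. The fields needed are already planned for the log. After the change, stage one tests acceptance among those approached while the final target concerns all eligible patients; the text should say that this difference is intended.

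### The confidence interval illustrated for an 8% VTE risk in 30 patients (0 to 19%) is centred too low: it should read about 2% to 23%

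*Protocol article*

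**What the plan says.** All the figures are in the protocol article, under RCT sample size calculation.

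For recurrent VTE, the text says "Thirty patients per arm will provide enough power to create a 95% confidence interval around the risk of VTE recurrence" and puts the width at 34% or less. Two examples follow. At a 50% risk in the arm that stopped, "we would be able to estimate a confidence interval of approximately 33% to 67% or smaller". Then: "If the risk of VTE were 8%, the confidence interval would be 0 to 19" (per cent). No interval method is named.

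For the proportion willing to be randomized, the section opens with "We anticipate there being at least 200 eligible patients per year in total from all three recruitment settings". It later reasons from "If we expect that 200 will be the maximum potential number of eligible patients" to a "95% confidence interval for the percentage willing to be randomized of width 13.7% or less". Three examples follow: "if the percentage is 50%, then we could expect the 95% confidence interval to be 43.15 to 56.85" (per cent) with 200 patients, 23.7 to 36.3% for a 30% rate with 200, and 42.1 to 57.9% for a 50% rate with 150.

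**The concern.** The 8% example looks wrong on its face. Eight per cent of 30 is 2.4 events, so the observed result would be two or three recurrences. A true risk of zero cannot produce even one, so zero does not belong in a two-sided interval from such data. A symmetric interval that has been cut at zero is also likely to sit too low at its upper end.

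The proportion with recurrent VTE is listed as a primary outcome, and the sample size section says that it will inform the phase three design. A reader who takes 19% as the upper limit would set aside risks of 20% to 23%, which two or three events in 30 do not rule out. The 8% example is also nearer than the 50% one to the only recurrence rates that the article cites (4.1% in the extended period and 11.1% overall, in an uncontrolled dalteparin study). Those are on-treatment rates; the article gives none for patients who stop.

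The second, smaller question is whether 200 is a floor or a ceiling. That decides whether 13.7% can be called an upper bound on the width.

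**Working it through.** **Inputs.** From the sample size section: n = 30 per arm with p = 0.08 and 0.50; n = 200 with p = 0.30 and 0.50; n = 150 with p = 0.50; 95% confidence. I use z = 1.96, so z² = 3.8416.

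**Step 1: reproduce 0 to 19%.**
- Plain Wald: 0.08 ± 1.96·√(0.08·0.92/30) = 0.08 ± 0.0971, or −1.7% to 17.7%. No match.
- Wald with continuity correction adds 1/(2·30) = 0.0167 to the half-width: −3.4% to 19.4%. Cut at zero, this matches.
- Agresti-Coull: adjusted size 30 + 3.8416 = 33.84; adjusted proportion (2.4 + 1.9208)/33.84 = 0.1277; half-width 1.96·√(0.1277·0.8723/33.84) = 0.1124. Placed around the raw 0.08, this gives −3.2% to 19.2%. Cut at zero, it also matches.

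**Step 2: see which route fits the other examples.** Entries are in per cent.

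| Case | Stated | Wald | Wald, continuity-corrected | Agresti-Coull half-width around raw p | Wilson |
|---|---|---|---|---|---|
| 50%, n = 200 | 43.15–56.85 | 43.1–56.9 | 42.8–57.2 | 43.1–56.9 | 43.1–56.9 |
| 30%, n = 200 | 23.7–36.3 | 23.6–36.4 | 23.4–36.6 | 23.7–36.3 | 24.1–36.7 |
| 50%, n = 150 | 42.1–57.9 | 42.0–58.0 | 41.7–58.3 | 42.1–57.9 | 42.1–57.9 |
| 50%, n = 30 | 33–67 | 32.1–67.9 | 30.4–69.6 | 33.2–66.8 | 33.2–66.8 |
| 8%, n = 30 | 0–19 | −1.7–17.7 | −3.4–19.4 | −3.2–19.2 | 2.5–23.1 |

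Of these, only the Agresti-Coull half-width around the raw proportion fits all five. In the first row its width is 2·1.96·√(0.25/203.84) = 13.73%; half of the rounded 13.7 is the 6.85 that the text uses. The continuity-corrected Wald interval fits the 8% case but gives a width of 39% at 50% of 30, against the stated 34%. Wilson fits the 50% cases but neither of the others.

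**Step 3: size of the shift.** The adjusted centre at 8% of 30 is 12.8%, so the printed interval sits 12.8 − 8.0 = 4.8 points too low. At 30% of 200 the adjusted centre is (60 + 1.92)/203.84 = 30.4%, a shift of about 0.4 points. At 50% the two centres coincide.

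**Step 4: properly constructed intervals at 8% of 30.**
- Wilson: centre 0.1277; half-width (1.96/1.1281)·√(0.0736/30 + 3.8416/3600) = 0.1031; 2.5% to 23.1%.
- Agresti-Coull, correctly centred: 0.1277 ± 0.1124; 1.5% to 24.0%.
- Clopper-Pearson, interpolated at 2.4 events: 1.3% to 23.9%.
- Jeffreys: 2.0% to 21.6%.
- Attainable results, exact: 2/30 gives 0.8% to 22.1%; 3/30 gives 2.1% to 26.5%.

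Against 19%, the upper limit is higher by 4.1 (Wilson), 4.9 (Clopper-Pearson) and 5.0 points (Agresti-Coull). Jeffreys gives the smallest gap, 2.6 points. Even 2/30, an observed risk of 6.7%, has an exact upper limit above 19%.

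**Step 5: the 13.7% width.** At n = 200 the width is largest at 50%, where it is 13.7%; at 30% it is 12.6%. At 50% with n = 150 it is 57.9 − 42.1 = 15.8%.

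**The case against.** The strongest reply is that little depends on this sentence. The examples are illustrations and set no sample size. The printed interval is 19 points wide against 20.6 for Wilson, so the fault is mainly one of position, and the general claim of a width of 34% or less survives (33.7% at 50%). One procedure appears to lie behind all five examples, so this is not a stray slip of arithmetic. All of that stands. It limits the importance of the point but does not make the printed limits right.

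A reader might also infer more than the documents support:
- That 13.7% is miscalculated, or is a best case presented as a bound. It is correct as the widest interval over all proportions at n = 200. The text gives the smaller interval at 30% and then the wider one for 150 patients, so nothing is hidden. If 200 is a minimum, the bound holds over the number of patients too. At the 30% target rate the Wilson width is still about 13.7% with roughly 170 patients.
- That the risk after stopping LMWH is made to look better bounded than it is. Only the 50% example is assigned to the arm that stopped; the 8% example is assigned to no arm.
- That the final analysis will use a poor interval. The examples do not fix the analysis method, and naming it is commonly left to the analysis plan, which is not shown.

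**Conclusion.** The point holds as a minor correction. The stated 0 to 19% is wrong as a 95% interval for 8% of 30: the lower limit should be above zero (about 1% to 2.5%, depending on method), and the upper limit is about 4 to 5 points too low by Wilson, Clopper-Pearson or correctly centred Agresti-Coull. The 30% of 200 example has the same fault at about 0.4 points. The 50% examples are sound.

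The mis-centred Agresti-Coull half-width is an inference from the fit to all five examples, since the article names no method. The conclusion on the 8% interval does not depend on it.

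On the number of eligible patients, the contradiction between 200 as a minimum and 200 as a maximum is real, but it is one of wording. No calculation changes because of it. Nor does any of this touch the 62-patient rule, the registration target of 200 or the aim of randomizing 60.

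**What to change.** - Replace the 8% interval with about 2% to 23% (Wilson). Because 8% of 30 is not a whole number of patients, it would help to add the attainable cases: 2/30, exact 0.8% to 22.1%; 3/30, exact 2.1% to 26.5%.
- Replace the 30% of 200 interval with about 24.1% to 36.7% by the same method. The 50% examples can stay.
- Describe 200 in one way throughout. State that the width is at most 13.7% with 200 eligible patients and wider with fewer, for example 15.8% at a 50% rate with 150.

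The cost is two corrected intervals and one reworded sentence. The only downside is that the stated upper limit for VTE risk becomes slightly less favourable.

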#### RCT data collection

Participants randomized to the RCT will be seen at the recruiting hospital clinical or GP practice (as appropriate) approximately 12 and 26 weeks after starting a further six months treatment with LMWH (treatment arm) or after stopping treatment with LMWH after six months treatment off-trial (control arm). Assessments will include VTE treatment and compliance, physical assessment, full blood count, urea, electrolytes, liver function test, bone profile, toxicities, concomitant medications, use of NHS resources (hospital admissions, GP visits, nurse visits: details to be taken from patient diary booklet and patient notes), and quality of life questionnaires (EORTC QLQ-C30, E5D-5 L and ESAS-r). VTE, bleeding events, and serious adverse events will be collected in real time. Adverse events, in particular the secondary outcomes of recurrent VTE or hemorrhagic events, will be monitored by the Independent Data Monitoring Committee. In the event of excessive bleeding or thrombotic events, this committee will advise on early closure of the trial if necessary. Research staff at recruiting sites will be expected to complete trial case report forms (CRFs) that record evidence of primary and secondary outcome measures. Patients will also be asked for optional consent to have their NHS number collected and to be registered with NHS Information Centre Flagging so that the date and cause of death can be collected without longer term follow up.

